# Effectiveness of acupuncture, special dressings and simple, low-adherence dressings for healing venous leg ulcers in primary healthcare: study protocol for a cluster-randomized open-labeled trial

**DOI:** 10.1186/1472-6882-8-29

**Published:** 2008-06-11

## Abstract

**Background:**

Venous leg ulcers constitute a chronic recurring complaint that affects 1.0–1.3% of the adult population at some time in life, and which corresponds to approximately 75% of all chronic ulcers of the leg. Multilayer compression bandaging is, at present, the only treatment that has been proved to be effective in treating this type of ulcer. There is no consensus, however, about the dressings that may be applied, beneath the compression, to promote the healing of this type of ulcer, as there does not seem to be any added benefit from using special dressings rather than simple, low-adherence ones. As well as analgesia, acupuncture provokes peripheral vasodilation, in skin and muscles – which has been demonstrated both experimentally and in clinical practice – probably due to the axon reflex, among other mechanisms. The aim of the present study is to measure the effectiveness and cost of compression treatment for venous leg ulcers combined with special dressings, in comparison with low-adherence ones and acupuncture.

**Methods/design:**

Cluster-randomized open-labeled trial, at 15 primary healthcare clinics in the Sevilla-Sur Healthcare District, with a control group treated with compression bandaging and low-adherence dressings; the experiment will consist, on the one hand, of the compression treatment applied in combination with special dressings (Treatment 1), and on the other, the compression treatment applied in association with low-adherence dressings, together with acupuncture (Treatment 2).

**Discussion:**

The results will be measured and recorded in terms of the median time elapsed until complete healing of the ulcer, and the rate of complete healing at 3 months after beginning the treatment. An economic analysis will also be made.

This study, carried out in the context of real clinical practice, will provide information for decision-taking concerning the effectiveness of special dressings. Moreover, for the first time a high-quality study will evaluate the effectiveness of acupuncture in the process of healing venous leg ulcers.

**Trial registration:**

Current Controlled Trials ISRCTN26438275.

## Background

Venous leg ulcers (VLU) constitute a chronic recurring complaint that affects 1.0–1.3% of the adult population at some time in life, and which corresponds to approximately 75% of all chronic ulcers of the leg [1]. They are caused by sustained venous hypertension, which is the result, in almost 50% of cases, from superficial venous insufficiency or from malfunctioning valves in perforating veins, with a normally-functioning deep venous system. Other factors that may result in sustained venous hypertension are those that impede the pumping function of the leg muscles, such as conditions that reduce spontaneous movements (Parkinson's disease, stroke, spinal cord injuries or excessive sedation). This type of chronic venous insufficiency is characterized by oedema, venous dilation, painful legs and stasis dermatitis. VLU patients have a worse quality of life than non-affected persons of the same age due to the pain, malodour and loss of independence that it causes [2]. The precise procedure by which hypertension leads to ulceration has yet to be clarified, but various mechanisms are known to be capable of intervening in its development and maintenance, such as plasma extravasation, pericapillary deposits of fibrin [3], disorders of the fibrinolytic system [4], the fixing or retention of growth factors by macromolecules in the dermis, or leukocytes in the veins of the legs [5-7].

In the USA, VLUs have been estimated to cost a billion dollars a year, representing an average cost of over 40,000 dollars during the lifetime of each patient [1], without taking into account the financial effects of impaired quality of life, sick leave and frequent hospitalization. In the United Kingdom, the average cost of treating venous ulcers varied between 814 to 1,994 euros per year, of which a large proportion is devoted to nursing expenses [8,9]. In Europe, the total cost of VLU treatment amounts to 1% of the annual healthcare budget [10], with an estimated mean cost of 250 euros in Spain per patient, per year of treatment [11].

Developing a healthcare plan for VLU patients includes curing active ulcers and preventing relapses. To achieve these goals, such a plan must address the treatment of infections associated with these ulcers, preventing the development of infection, stimulating granulation and epithelial tissues, compression, raising the leg position, improving mobility, reducing obesity, improving nutrition and, in some cases, performing surgery [12,13].

Perhaps the most controversial aspect of the local treatment of VLUs concerns the type of dressings to use [14]. The use of wet dressings has been shown to favour granulation and epithelialization processes and, therefore, the healing of the ulcer, but no evidence has been provided to assist in choosing between special dressings and simple, low-adherence ones [15]. The application of external compression causes various complex physiological and biochemical effects that affect the venous, arterial and lymphatic systems. Provided the degree of compression does not adversely affect arterial blood flow, and that the correct techniques and materials are applied, the effects of compression may be very positive, reducing oedema and pain, whilst at the same time favouring the healing of ulcers caused by venous insufficiency. However, there are many ways in which this compression may be applied, and there is no consensus as to which is best [16]. Depending on the size of the ulcer, healing rates with compression treatment range from 40–70% at three months to 50–80% at 6 months [17,18]. The latest systematic review carried out by the Cochrane Collaboration recommends compression therapy and low-cost, low-adherence dressings as a first-line treatment for healing VLUs [15].

In addition to analgesia, acupuncture provokes peripheral vasodilation in the skin and in muscles, probably due to the axon reflex [19-21]. Stimulation of Aδ and C fibres releases vasoactive neuropeptides, as well as proinflammatory agents like the calcitonin gene? related peptide (CGRP), the P substance (SP), neurokinin A (NKA), opioids, galanin, somatostatin and vasoactive intestinal peptide (VIP) [22,23]. Deep, prolonged vasodilation may also be mediated by CGRP [24-26]. Some studies have suggested that the neuropeptides released by sensory nerve stimulation are beneficial in maintaining skin integrity [23,27,28], for healing ulcers [29,30] and for peripheral vascular disorders [31,32]. Another key element in regulating the vascular tone and the blood flow is the endothelial synthase of nitric oxide (NO), which is responsible for catalyzing the NO [33], which is active in arteriolar vasodilation and reduces peripheral resistance, facilitating normal blood flow to the tissues [34]. It has been shown that the expression of NO-synthase (NOS) is greater in skin regions where acupuncture points and channels are located. In these areas, moreover, there are raised levels of NO in the blood after acupuncture [35,36], which suggests that the acupunctural stimulation of the sensorial nerves may act as an *in vivo *modulator of NO levels [32]. Although studies have been carried out to examine the effectiveness of acupuncture in treating VLUs, these have been of poor quality and have reported contradictory results [37-39].

In this paper, we propose a multicentre cluster-randomized study, with a predetermined sample size, and appropriate follow up, assessing the patients' quality of life and employing an objective results measure that will enable us to accurately evaluate the length of time needed for patients' ulcers to heal, thus meeting the recommendations of the Cochrane Collaboration's review body [15,16].

## Methods/Design

### Research aims and questions

The aim of this study is to determine whether the combination of compression bandaging with simple, low-adherence dressings and acupuncture is more effective than when the same bandaging is employed in combination with special dressings or with simple, low-adherence dressings, but no sensory stimulation (acupuncture), with respect to the complete healing of venous leg ulcers.

The following research questions are proposed:

▪ In terms of the healings of venous leg ulcers, is it better to employ compression bandaging associated with sensory stimulation (acupuncture) and simple dressings, than the same bandaging without sensory stimulation, with special dressings, or than the compression bandaging without sensory stimulation and with simple dressings?

▪ What are the differences between healing treatments with special dressings and those with simple, low-adherence ones, in terms of the complete healing of venous leg ulcers?

▪ How long does it take for venous leg ulcers to recur?

▪ How effective is the treatment in terms of reducing pain intensity?

▪ How effective is the treatment in terms of reducing the amount of analgesic and anti-inflammatory medicines consumed?

▪ Are there any quality of life changes related to the health of patients with venous leg ulcers?

▪ What is the total financial cost of each of the treatments studied?

▪ What is the cost-effectiveness ratio of the treatments studied, for patients with venous leg ulcers?

▪ What is the opportunity cost of treatments not implemented?

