#### Secondary outcome variables

##### Complete healing at 3 months after beginning treatment

Complete healing is defined as the complete epithelialization of all the leg venous ulcers, not just the reference one (table 1).

**Table 1 T1:** Outcome measures. Work scheme with description of assessment visits and times.

	**Baseline (T0)**	**Weekly treatment**	**Evaluation at 3 months (T1)**	**Weekly treatment (if necessary)**	**Evaluation at 6 months (T2)**	**Evaluation at 12 months (T3)**
Sociodemographic data	X					
Ankle/arm index	X					
Nutritional study	X					
Localization of ulcer(s)	X		X		X	X
Area of main ulcer	X	X	X	X	X	X
Duration of the main ulcer	X					
Exudate culture (if necessary)	X	X	X	X	X	X
Changes in the size of the main ulcer		X	X	X	X	X
Characteristics of the main ulcer	X	X	X	X	X	X
Complete healing (date)		X	X	X	X	X
Pain intensity		X	X	X	X	X
SF-12	X		X		X	X
Adverse events/effects		X	X	X	X	X
Compliance with hygiene-posture recommendations	X		X		X	X
Location of treatment (clinic/home)		X		X		
Time employed in treatment		X		X		
Materials employed in treatment		X		X		
Number of needles used(Group A)		X		X		
Obtention of Deqi (Group A)		X		X		

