##### Pain intensity measured on a visual analogue scale

There exists sufficient evidence to corroborate the validity of the visual analogue scale of pain intensity. Many studies have demonstrated the validity of the concept [46] and its reliability [47,48]. With this method, the subjective intensity of pain may be measured quickly and straightforwardly. The patient is asked to mark the degree of pain intensity on a millimetric scale, from 0 (no pain) to 100 (the worst pain imaginable).

**Changes in the health-related quality of life **at 3, 6 and 12 months (12-item Short Form health survey, version 2) [49].

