#### Covariables

The covariables recorded will be the patient's age, sex, educational level, occupation, income, weight (kg), height (cm), mobility, systolic arterial pressure, diastolic arterial pressure, arm/ankle index and ankle diameter (cm), the duration of the active ulcer (weeks), the location of the ulcer (if more than one ulcer is present, stating the location of the largest one, which is taken as the reference ulcer), whether the ulcer is unilateral or bilateral, the number of ulcers on the leg(s), whether the ulcer is new or recurrent (in the latter case, recording the time since the first appearance, in years and months), the signs of granulation at the base of the ulcer, the signs of epithelialization at the edges of the ulcer, the presence of fibrinous and/or necrotic tissue, the presence of lipodermatosclerosis, and the presence of infection. Other variables recorded will include dependence on tobacco, alcohol or other psychoactive substances, the presence of diabetes mellitus, the results of a nutritional study (haemogram and biochemical tests: albumin, prealbumin, transferrin and proteinogram), the time elapsed until recurrence occurs (weeks), compliance with hygiene-posture recommendations, self care, and the assistance or otherwise of non-professional carers. In addition, a record will be kept of all medication taken (corticoids, immunosuppressors, anticoagulants, etc.) and information about possible cultures of the ulcer exudate.

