### Measurements (measurement times)

#### Baseline evaluation basal (T0)

▪ The data obtained in the examination made prior to beginning treatment will include personal and sociodemographic characteristics, background and case history, ankle/arm index, nutritional status, previous treatment received, results of the ulcer exudate culture, the dimensions of the ulcer and observations regarding its condition, location and duration in an active state, as well as about the patient's health-related quality of life.

▪ Follow up. At each visit, the nurse applying the treatment will record the macroscopic status of the ulcer, any adverse events that may have occurred, the time employed in providing the treatment, the location of the treatment (clinic/home) and the name of the person performing it. If total healing of the ulcer is detected during a routine examination, the treatment programme official at the relevant Clinic should be informed. For the patients in Group A, a record should also be kept of the data concerning the acupuncture session (the number and location of local points).

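### The pain scale is not scheduled at baseline, so reduction from a pre-treatment score cannot be calculated and imbalance in initial pain can be neither checked nor adjusted for

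*Protocol article*

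**What the plan says.** Among the research questions in the protocol article (Research aims and questions) is "How effective is the treatment in terms of reducing pain intensity". Under Secondary outcome variables the outcome is named "Pain intensity measured on a visual analogue scale", scored from 0 to 100, with no measurement times given there.

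The times are in Table 1 (Outcome measures). The pain row reads "Pain intensity X X X X X": five marks across six columns, with the Baseline (T0) cell empty. The row for ulcer size reads "Area of main ulcer X X X X X X", with T0 marked. SF-12 is marked at T0, T1, T2 and T3.

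The text on the baseline evaluation begins "The data obtained in the examination made prior to beginning treatment will include personal and sociodemographic characteristics, background and case history, ankle/arm index, nutritional status" and closes with "as well as about the patient's health-related quality of life". Pain does not appear in between. The list under Covariables, which starts "The covariables recorded will be the patient's age, sex, educational level, occupation, income, weight (kg), height (cm), mobility", does not contain pain either.

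**The concern.** A question about reducing pain is most naturally answered with a score taken before treatment and scores taken after it. This schedule collects only the later ones. What is never collected cannot be recovered in an analysis plan, so this is a matter of data collection and not of analysis detail left for later.

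Two things are at stake. First, a patient's reduction from the pre-treatment level cannot be calculated. Second, the Data analysis section plans to compare the groups at baseline and to adjust for unbalanced variables in a multilevel model, and that safeguard cannot reach a variable without a baseline value. The design gives the second point some weight: whole clinics are allocated, there are five per arm, and patients enter by seeking care at a participating clinic, so differences in case-mix between clinics pass into the arms.

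**Working it through.** **Is the blank cell real?** The extracted table could have lost a column, so I compared rows.
- Ulcer area has six marks for six columns, T0 included.
- SF-12 has marks at T0, T1, T2 and T3 and gaps at the two weekly columns.
- Pain has an empty T0 cell and marks in all five later columns.
- The other rows with no T0 mark are change in ulcer size, date of healing, adverse events, and treatment-session items (location, time, materials, needles, Deqi). None of these has a pre-treatment value. Pain is the only row left blank at T0 for which one exists.

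The columns align, and the T0 text and the covariable list agree with the table.

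**Can the first weekly score stand in?** Three sections bear on this.
- Data collection: the treating nurse's routine assessment takes place once cleansing is done.
- Interventions: in Group A, acupuncture is delivered in the same session as cleansing.
- Acupuncture (Study Group A): the needles go in after cleansing.

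The order of scoring and needling within the session is not fixed, so the first score in Group A may follow the first needling. The Background attributes analgesia to acupuncture and says that compression may reduce pain. Nothing says that the first weekly score is taken before treatment or counts as baseline. Used as a baseline, it could absorb part of the effect in one arm only.

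**Size (illustration only).** The plan gives no figure for pain, so there is none to reproduce.

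Inputs from Sample size: 125 patients per arm, 5 clinics of 25, intra-cluster correlation (ICC) 0.05. That ICC is stated for healing; applying it to pain is my assumption, so a range is shown.

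Design effect = 1 + (25 − 1) × ICC. SD of the chance difference between two arms in mean baseline pain = sqrt(2 × design effect / 125), in units of the patient-level SD.

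| ICC for pain (assumed) | Design effect | SD of chance difference | Probability of a difference above 0.2 SD |
|---|---|---|---|
| 0.01 | 1.24 | sqrt(2 × 1.24/125) = 0.14 | 16% |
| 0.05 | 2.20 | sqrt(2 × 2.20/125) = 0.19 | 29% |
| 0.10 | 3.40 | sqrt(2 × 3.40/125) = 0.23 | 39% |

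For reference, individual randomisation of 125 per arm would give sqrt(2/125) = 0.13.

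**Precision.** With correlation r between baseline and follow-up pain, the sample needed without the baseline, relative to an analysis adjusted for it, is 1/(1 − r²):
- r = 0.3: 1/0.91 = 1.10
- r = 0.5: 1/0.75 = 1.33
- r = 0.7: 1/0.51 = 1.96

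These correlations are assumptions, and the formula is for individual patients. In a comparison of five clinics per arm the gain also depends on how clinic means correlate over time, which the document does not give.

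**The case against.** The strongest reply is that the trial does not need baseline pain to estimate a treatment effect. The arms are randomised, and pain is scheduled at 3, 6 and 12 months in all of them. A comparison at those times answers whether one treatment leaves patients with less pain than another. The outcome is also named as a level, whereas ulcer size and quality of life are named as changes and do have T0 values. On that view the schedule fits the outcome definition, and the mismatch is with one word in a research question. This stands, and it limits the point.

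A reader might infer that the plan cannot answer its pain question at all. The document does not support that: the comparison of follow-up levels remains, though it is less precise and differs from reduction from a pre-treatment value.

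A reader might also infer that chance differences in initial pain would pass for a treatment effect. That does not follow either. Chance imbalance is sampling error in a randomised comparison, and an analysis that respects clustering carries it in the confidence interval.

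Nor does the document present pain as the main target of acupuncture. The stated aim is healing, and the rationale in the Background rests mostly on vasodilation.

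Finally, the T0 list may not be exhaustive, the data form is not shown, and an article condenses. The follow-up text omits pain as well, so the lists alone would be weak evidence. Table 1, however, sets out each measurement by visit and leaves this one cell empty, so this reply has little force.

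**Conclusion.** The point holds in a limited form. Pain is scheduled at every time except before treatment, and the first weekly score is not a clean replacement. Reduction from a pre-treatment value cannot be calculated, and imbalance in initial pain can be neither examined nor adjusted for. What remains is a valid but less precise comparison of follow-up levels.

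The size is moderate. The SD of a chance baseline difference is about 0.14 to 0.23 SD for an assumed ICC of 0.01 to 0.10. The sample penalty for a follow-up-only analysis is about 1.1 to 2.0 times for an assumed individual-level correlation of 0.3 to 0.7. The empty cell itself rests on no assumption.

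Only this secondary outcome is touched. Time to healing, healing at 3 months and the sample size calculation are not affected.

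**What to change.** Mark the pain VAS in the Baseline (T0) column of Table 1 and add it to the list under the baseline evaluation, stating that it is recorded before any study treatment. Analyse later pain with T0 pain as a covariate and clinic as a random effect, and include T0 pain in the planned baseline comparison.

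The cost is one VAS mark per patient at a visit that already takes place. No other outcome, visit or sample size figure changes. If some patients have already started treatment without a T0 score, report the follow-up comparison for all patients and do not relabel the first weekly score as baseline.

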### Design

Open-labeled, controlled multicentre prospective study, with random cluster allocation to treatment groups (Primary Healthcare Clinics) in the Sevilla-Sur Health District (Andalusian Public Health System).

### Study duration

April 2008-December 2010

### Subjects

#### Target population

patients with venous leg ulcers who request treatment at the Primary Healthcare Clinic.

#### Study population

patients with venous leg ulcers who request treatment by a healthcare professional (doctor or nurse) at one of the Primary Healthcare Clinics in the Sevilla-Sur Health District taking part in the study, with at least one active venous leg ulcer (open, CEAP C6 [40] with a diameter exceeding 1 cm.

Patients with one or more of the following will be **excluded **from the study:

▪ Arterial pathology (systolic pressure in the ankle of less than 80 mm Hg or ankle/arm systolic index less than 0.8).

▪ Diabetic ulcer of the foot, rheumatoid arthritis or systemic vasculitis.

▪ Use of anticoagulants

▪ Pregnancy

#### Sampling units

the Primary Healthcare Clinics participating in the study.

#### Analysis units

per Healthcare Clinic (according to the group assigned) and per patient.

#### Randomization and blinding procedure

a list of random numbers will be created, using statistical software, to which the researchers involved in the study will not have access. This list will be applied to the list of participating Clinics until the clusters for each group are obtained. Three types of cluster will be used, according to the treatment for the venous leg ulcer provided at the Clinic (**A: **compression therapy plus simple, low-adherence dressings and acupuncture; **B: **compression therapy plus special dressings; **C: **compression therapy plus simple, low-adherence dressings). Before beginning, the list of Clinics will be randomly ordered, by drawing lots blindly, with no repetitions, from a bag containing the names of all the Clinics taking part. None of those participating in this process will belong to the research group, and none of them will play any further part in the study.

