### Ethical criteria

The ethical validity of this study has been analyzed and approved by the Andalusian Government Committee for Clinical Trials, following the approval of the corresponding Research Commission at each of the participating Clinics. The study design takes into account the fundamental principles set out in the Helsinki Declaration, and those of the Council of Europe Convention concerning human rights and biomedicine, as well as the requirements under Spanish law in the field of biomedical research, the protection of personal data, and bioethics. All the patients involved must sign their informed consent to the proposed clinical research procedures. During the course of the study, audits will be performed as required by the relevant Research and Ethics Committee, as well as those of each Clinic's Quality Committee, independently of any external audits (such as that of the research financing body) that may be necessary.

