### Sample size

The sample size has been calculated following the parameters of Campbell et al. [41], on the basis of historical data [18]. The success rate for complete healing of venous leg ulcers at 3 months, with compression bandaging plus special dressings, is 44%. With an alpha (significance) level of 0.05 and a power of detection of differences of 80%, assuming a two-tailed approach, the total sample size needed will be 375 patients, in order to detect differences of 15% between the groups, as regards the rate of complete healing of venous leg ulcers at 3 months. This calculation assumes a possible dropout rate of 5% and an intra-cluster coefficient of correlation of 0.05 (according to the expected variance of the response within a single cluster). There will be 15 clusters (Primary Healthcare Clinics) and so each Clinic will need to recruit 25 subjects. Therefore, 3 treatment arms will be formed, with 125 patients in each (with 5 Clinics per arm).

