### Data collection

The routine follow-up evaluation, to be made following cleansing session, will be performed by the nursing staff responsible. The baseline evaluation (T0), that of the results at 3 months (T1), and the follow-up evaluations at 6 and 12 months (T2 and T3) will be carried out by the healthcare personnel responsible for the treatment programme (and who will be blinded with respect to the group to which each patient is assigned).

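### Patient entry is not shielded from knowledge of the arm: open, single-treatment clinics appear to recruit their own patients, and the only stated remedy is adjustment that depends on observed imbalance

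*Protocol article*

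**What the plan says.** - **Openness and unit of allocation.** The Design section describes an open-label trial with clinics as the allocated units. Under Randomization and blinding procedure, "Three types of cluster will be used, according to the treatment for the venous leg ulcer provided at the Clinic", so each clinic delivers one arm. The random list is applied to clinics: "This list will be applied to the list of participating Clinics until the clusters for each group are obtained".
- **Concealment.** The list is withheld from the researchers and outsiders draw the clinic order by lot: "None of those participating in this process will belong to the research group, and none of them will play any further part in the study".
- **Entry of patients.** Study population defines them as "patients with venous leg ulcers who request treatment by a healthcare professional (doctor or nurse) at one of the Primary Healthcare Clinics" taking part. Sample size adds "so each Clinic will need to recruit 25 subjects". Ethical criteria requires individual consent: "All the patients involved must sign their informed consent to the proposed clinical research procedures".
- **Baseline assessment.** Data collection gives the T0 evaluation to the staff responsible for the treatment programme, "who will be blinded with respect to the group to which each patient is assigned".
- **Handling of imbalance.** Data analysis compares baseline variables by group and carries forward only differences of clinical relevance. It then plans a multilevel analysis, with patients within clinics, to adjust for variables that turn out unbalanced. The main analysis is described as Kaplan-Meier, log-rank and Cox regression.

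**The concern.** In a cluster trial, allocation of clusters can be perfectly concealed while entry of patients is not. Once a clinic knows its treatment, it knows the treatment of everyone it might enrol. Staff can then, without any bad faith, approach or pass over patients according to how suitable that treatment seems. Patients can likewise accept or decline consent according to what is offered. Either would make the case mix differ by arm for reasons other than chance.

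Randomising clinics does not protect against this, because the selection happens after the draw. An intention-to-treat analysis does not repair it either: it keeps everyone who was enrolled but cannot restore those who were not. A larger sample would estimate the biased contrast more precisely. What is at stake is whether a difference in healing between arms can be attributed to the treatments.

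**Working it through.** No figure in the plan bears directly on this point, so the check is mainly a comparison of sections, followed by an illustration of size.

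**1. Who knows what at entry.** The trial is open-label (Design), each clinic has one treatment (Randomization and blinding procedure), patients enter by seeking care at a participating clinic (Study population), and the clinic recruits its own 25 (Sample size). Together these imply that the recruiting staff know the arm when they judge eligibility and ask for consent.

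**2. What the concealment covers.** The hidden list and the outside draw prevent anyone from steering a clinic into an arm. They have no effect on which patients are enrolled afterwards.

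**3. Whether blinded T0 assessment answers the point.** The blinding statement concerns assessment, not the decision to enrol. It is also hard to square with the rest of the article. The Acupuncture section has the programme head coordinate treatment, and the Measurements section places the programme official at the relevant clinic. At a single-treatment clinic, knowing the clinic means knowing the arm.

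**4. What eligibility leaves open.** Study population fixes an active ulcer over 1 cm in diameter, arterial limits and a few exclusions. Ulcer size above 1 cm, duration, recurrence and willingness to take part can still vary by arm.

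**5. What the analysis corrects.** The adjustment in Data analysis is triggered by the imbalance observed and limited to recorded variables judged relevant. Baseline ulcer area (Changes in the size of the surface area of the ulcer) and duration (Covariables; Baseline evaluation) are both collected. Neither is named as a covariate that will always be in the model.

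**6. Illustration of size.** Inputs:
- 3-month healing under compression of 40% to 70% depending on ulcer size (Background);
- target difference of 15 points and 25 patients per clinic (Sample size);
- assumption: two strata healing at 40% and 70%;
- assumption: the arms differ by d in the share of patients in the better stratum.

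If an arm has share s in the better stratum, its healing rate is 40 + 30 × s. With no treatment effect, the difference between two arms is 30 × d, whatever s is.

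| d (assumed) | Patients per clinic of 25 | Spurious difference | Share of 15-point target |
|---|---|---|---|
| 0.10 | 0.10 × 25 = 2.5 | 30 × 0.10 = 3 points | 3/15 = 20% |
| 0.20 | 0.20 × 25 = 5 | 30 × 0.20 = 6 points | 6/15 = 40% |
| 0.30 | 0.30 × 25 = 7.5 | 30 × 0.30 = 9 points | 9/15 = 60% |

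These are unadjusted differences in the 3-month healing proportion, which is a secondary outcome. The primary outcome is time to healing, for which the article gives no comparable spread.

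**The case against.** The strongest reply is that much of this rests on what a condensed article leaves out. The order of clinic allocation, consent and T0 is not stated in one place. Some wording even speaks of patients being randomised, and the flow diagram is not available. A screening log or a consecutive-enrolment rule may exist in a fuller protocol. This stands in part: the sequence is an inference, and the absence of a log is not in itself an error. The stated features (open label, one treatment per clinic, recruitment by that clinic) and the conditional adjustment rule do not depend on it.

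A reader might infer that nothing in the plan limits differences in case mix. That goes too far. Eligibility is uniform and partly objective, prognostic covariates are recorded, ulcer area is traced digitally, and a multilevel adjustment is planned. These limit or partly correct imbalance; they do not prevent selection at entry.

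A reader might also infer that allocation itself was open, or that selection would favour a particular arm. The draw was concealed, and nothing in the document points to a direction.

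Finally, one might turn the 3 to 9 points into an inflated type I error. The documents do not support that step. The shift is assumed, the strata are the extremes of a literature range, the outcome is secondary, no adjustment is allowed for, and a normal reference with five clinics per arm is only approximate.

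**Conclusion.** The concern holds in a limited form. As described, clinics with a known, single, open-label treatment appear to recruit their own patients, and the concealment covers clinics only. The one stated remedy is after the fact, depends on the imbalance observed, and cannot reach unmeasured factors. The Discussion lists three shortcomings of the design, and this is not among them.

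The conclusion rests on the inference that patients are identified and consented after their clinic's arm is known. The size cannot be determined from the document. The range of 3 to 9 points is an illustration under the two assumptions stated, not an estimate of the bias. The documents do not show that selective entry will occur. They show that the plan as written allows it, and that the correction for it is left to depend on the data.

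**What to change.** 1. **Data analysis.** State that baseline area of the main ulcer and its duration enter the primary time-to-healing model as fixed covariates, with clinic-level clustering, regardless of observed imbalance. Both are already collected at T0, so this needs no new data. It replaces a data-dependent choice of covariates with one fixed in advance. It does not deal with unmeasured factors.
2. **Study population.** State that all eligible patients are to be enrolled consecutively. Have each clinic keep a short log with ulcer area, ulcer duration and the reason for non-enrolment. Report numbers screened, eligible and enrolled by arm.

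The cost is slight paperwork per clinic. The log reveals and limits selective entry but does not fully prevent it. Listing patients and completing T0 before the draw is disclosed would protect those patients better. However, T0 includes blood tests, the SF-12 and a culture where needed, so it would require earlier consent and a separate baseline round. It would not help patients who present later. It is therefore costlier, less clearly feasible, and not needed for the two changes above.
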